## Abstract

**Background:**

Psychologically informed rehabilitation programmes such as the Progressive Goal Attainment Program (PGAP) have the potential to address pain-related disability by targeting known psychological factors that inhibit rehabilitation progress. However, no randomised controlled trials of this intervention exist and it has not been evaluated in the Irish health service context. Our objective was to evaluate the clinical efficacy and cost-effectiveness of the PGAP in a multicentre randomised controlled trial with patients who are work-disabled due to back pain.

**Methods and design:**

Adult patients (ages 18 years and older) with nonmalignant back pain who are work-disabled because of chronic pain and not involved in litigation in relation to their pain were invited to take part. Patients were those who show at least one elevated psychosocial risk factor (above the 50^th^ percentile) on pain disability, fear-based activity avoidance, fatigue, depression or pain catastrophizing. Following screening, patients are randomised equally to the intervention or control condition within each of the seven trial locations. Patients allocated to the control condition receive usual medical care only. Patients allocated to the PGAP intervention condition attend a maximum of 10 weekly individual sessions of structured active rehabilitation in addition to usual care. Sessions are delivered by a clinical psychologist and focus on graded activity, goal-setting, pacing activity and cognitive-behavioural therapy techniques to address possible barriers to rehabilitation.

The primary analysis will be based on the amount of change on the Roland Morris Disability Questionnaire posttreatment. We will also measure changes in work status, pain intensity, catastrophizing, depression, fear avoidance and fatigue. Outcome measures are collected at baseline, posttreatment and 12-month follow-up. Health-related resource use is also collected pre- and posttreatment and at 12-month follow-up to evaluate cost-effectiveness.

**Discussion:**

This study will be the first randomized controlled trial of the PGAP in chronic pain patients and will provide important information about the clinical and cost effectiveness of the programme as well as its feasibility in the context of the Irish health service.

**Trial registration:**

Current Controlled Trials: ISRCTN61650533

## Background

Back pain constitutes a major health problem. In Ireland, between 13% and 36% of the population have chronic pain, with back pain being the most frequently reported site of pain [1,2]. Importantly, of those who consult their general practitioner (GP) for chronic pain, 60% to 80% still have pain and disability 1 year later [3,4]. The economic burden associated with chronic pain is also considerable. Recent research has estimated the cost of chronic pain at €5.34 billion, or 2.86% of gross domestic product per year in Ireland [5], with a large proportion of these costs being attributable to wage replacement for those unable to work because of back pain. Over the past decade, research has consistently highlighted the importance of psychological factors in the development and maintenance of back pain disability [6]. Specifically, fear avoidance beliefs [7], low mood [8] and a cognitive process known as catastrophizing [9] are consistently related to poor outcome [10,11]. There is evidence that these variables may play an important role in maintaining disability beyond the expected recovery time for soft-tissue injury and may be significant barriers to activity involvement and successful rehabilitation [12].

Although some reviews have shown only modest results for the success of interventions that target psychosocial risk factors [10,13], improvements in patient outcomes have been demonstrated when subgrouping has been used to guide treatment [14,15]. This subgrouping, or ‘matching’, of patients to different treatment options on the basis of psychological risk factors [14] has demonstrated that psychologically informed management can result in both health and economic benefits.

One such psychologically informed pain rehabilitation programme is the Progressive Goal Attainment Program (PGAP) [12,16]. PGAP and its predecessor the Pain Disability Prevention (PDP) program (under which name this trial was originally registered) were designed in Canada to reduce long-term disability arising from pain and other health conditions. PGAP is a manual-driven, 10-week rehabilitation programme designed to target evidence-based psychosocial risk factors for pain-related disability. These risk factors include fear-avoidance beliefs, pain catastrophizing, perceived injustice and depression. One of the most important components of this programme is activity mobilization. It has been acknowledged [12], however, that the predominately physical conceptualization of activity mobilisation may account for the relative lack of rehabilitation success for some patients [17]. Therefore, the role of psychological factors in facilitating and impeding activity mobilisation may have been underestimated. It has been argued [12] that activity mobilization is a form of behaviour change, one that involves a complex interplay among several psychological variables. The incorporation of psychological techniques to promote activity mobilisation is the basis for the PGAP.

The PGAP has proven efficacy in reducing disability and promoting return to work among people with work-related musculoskeletal pain [16] and whiplash injury [18]. However, there has not yet been a randomized controlled trial of PGAP in a chronic pain population. Thus, there is a need for an RCT study in which this rehabilitation programme (plus usual medical treatment) is compared to usual medical treatment alone. In addition, the PGAP has been developed in the context of a highly systematic and structured worker’s compensation system in Canada, but Ireland does not have a formal worker’s compensation system or rehabilitation case management. There is also very little access to psychologically informed back pain interventions at a community level in Ireland. Most routine pain management is provided by primary care GPs and physiotherapists who work in the public and private sectors and generally offer generic treatment services. However, there are virtually no other community-based pain management services in Ireland. Ireland does not have a national policy on the management of pain, nor does it have any general practice guidelines for the management of pain [19]. In the absence of a systematic pain management infrastructure in the community, the evaluation of a service that could be provided over and above normal primary care provision would seem highly valuable.

The present study was designed to examine the effectiveness of this psychologically based rehabilitation programme with a view to bridging this gap in service provision. We also propose to conduct a qualitative study with those receiving PGAP and the primary referral sources to get feedback on the user-friendliness of the programme, since establishing the feasibility of the programme is a specific objective.

The rationale for an economic evaluation of the PGAP is evident when one looks at the costs of long-term pain and associated disability [2,20]. Even a small reduction in the number of people with chronic disability is expected to be highly cost-effective and to greatly reduce the personal burden on those affected by chronic pain [20,21]. The study proposed herein will include a detailed cost–benefit analysis of the intervention as well as an analysis of its cost-effectiveness in terms of any cost savings associated with reduced disability. This will include an evaluation of both direct and indirect costs.

In summary, the study described herein has the following aims: (1) to examine the feasibility of implementing a community-based psychological pain rehabilitation programme (PGAP) aimed at treating patients who show elevated psychosocial risk factors for long-term pain-related disability, (2) to assess the effectiveness of the programme in a randomised controlled trial comprising PGAP plus medical treatment as usual (MTAU) versus MTAU only, (3) to determine the costs and cost savings associated with the programme by utilising appropriate indicators of health-related costs, (4) to gather feedback about the programme from key stakeholders and (5) to determine whether any changes achieved as a result of the programme are maintained at 12-month follow-up.

## Methods and design

This PGAP study is a pragmatic, multicentre randomised controlled trial of a cognitive behavioural therapy–based active rehabilitation programme for patients who are work-disabled due to back pain.

### Setting

The trial intervention is delivered by clinical psychologists based in eight regions of the Republic of Ireland: Galway, Mayo, Sligo, Donegal, Limerick, Cork and Dublin. The coordinating centre is the Centre for Pain Research at the National University of Ireland, Galway (NUI Galway), involving the academic departments of psychology, general practice, economics and the HRB Clinical Research Facility Biostatistics Unit. The intervention programme, PGAP, is delivered by public sector clinical psychologists based in each region. However, trial management and data collection take place at the Centre for Pain Research at NUI Galway.

### Hypothesis

The primary objective of the present study is to evaluate whether patients with back pain who take part in the PGAP (intervention group) show a greater mean reduction in reported disability compared to those who receive MTAU only (control group). Secondary objectives are (1) to examine changes in work status postintervention among those in the intervention group compared with the change in those in the control group (2) to examine changes in psychological variables among those in the intervention group compared to those in the control group and (3) to examine the cost-effectiveness of the programme to assess whether the costs of treatment are less than the savings associated with better outcomes.

### Recruitment and eligibility

#### Recruitment

Potential participants are recruited directly from GPs and via self-referral (Figure 1). GP practices in Galway, Sligo, Limerick, Donegal, Cork, Mayo and Dublin were approached and informed about the study. The trial was also advertised in the local media at each trial location and within physiotherapy and primary care practices. These announcements offered patients the option to contact the research team directly if they were interested in taking part in the trial. Patients who contacted the research team directly were initially interviewed briefly over the phone by the researcher involved in the trial. Those who fit the initial inclusion criteria (see below) were given a brief explanation of what the trial involved and were then sent a detailed information leaflet explaining all aspects of the trial. The information leaflet also contained two consent forms, one to be signed by the patient and one to be signed by the patient’s GP. Patients were asked to bring this information leaflet and the consent form to their GPs. Each GP was asked to sign the consent form to confirm the patient’s medical suitability to take part in the trial.

**Figure 1 F1:**
[figure not shown]
Flowchart of patient recruitment.

Patients who are referred to the trial by their GP are given the information leaflet and consent form, as described above, by their GP at consultation. Both consent forms are then returned to the research team. When the research team receives the signed consent form from both patient and GP, formal assessment measures are then sent to the patient to screen for the presence of elevated psychosocial risk factors.

#### Inclusion criteria

Participants are patients with nonmalignant back pain 18 to 65 years of age who are not working or working no more than 50% of their usual work hours because of nonmalignant back pain. Back pain must be present for at least 6 weeks. GPs must confirm the presence of the painful condition and approve their patients’ participation in an activation programme.

#### Exclusion criteria

Patients are not eligible to participate in the trial if they meet any of the following exclusion criteria. (1) The GP confirms the presence of ‘red flags’ indicating serious pathology (for example, cancer, fracture, infection). (2) The patient has serious cognitive and psychiatric comorbidity. This criterion will include patients who have a diagnosis of a serious axis 1 or axis 2 mental health disorder as defined by the *Diagnostic and Statistical Manual of Mental Disorders, Fourth Edition* (DSM-IV). (3) The patient has a cognitive impairment that may affect the ability to engage in the programme (for example, Alzheimer disease, aphasia, stroke). The presence of these conditions will be confirmed by the patient’s GP. (4) The patient is currently receiving psychological management for pain. (5) The patient is involved in litigation in relation to the injury.

### Ethical approval

The final study protocol and the final version of the written informed consent form were approved by the NUI Galway Research Ethics Committee (Ref 09/NOV/10). Approval was also granted by individual hospital ethics committees at each trial site. The procedure set out in this protocol was designed to ensure that all persons involved in the trial abide by good clinical practice and by the ethical principles described in the current revision of the Declaration of Helsinki. Patients are required to sign a written consent form before being admitted to the clinical trial. The patient’s GP must also consent that the patient is medically suitable to take part in the research.

### Sample size

Following published guidelines [22], the sample size calculation was based on having 80% power at the 5% significance level to detect a difference in mean post-treatment improvement of 3 units or more on the Roland-Morris Back Pain Questionnaire between the control and intervention groups, assuming that the standard deviation of the improvement is 6.1 units in both groups [14]. In order to ensure sufficient power to detect such a difference, a sample size of 60 is needed for each arm. However, allowing for an attrition rate of 15% [16], and based on the experience of [name] *et al*. (personal communication [name], September 2007), we aim to include 140 participants (70 per group) in the study and expect to have complete data for about 120 participants following dropouts.

Screening of larger numbers of patients will be required to obtain a sample of 140. On the basis of recent research examining the prevalence of psychosocial risk factors among a general practice population, where at least one factor was found in 24% of respondents and up to 52% had a particular risk indicator, we expect that 20% to 50% of our sample frame will have one or more of the psychosocial risk factors [23].

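### The stated 60 per arm gives about 76% power, not 80%, for a 3-point difference with SD 6.1; 80% needs 65 to 66 per arm analysed (two-sided, unadjusted)

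*Protocol article*

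**What the plan says.** The Sample size section of the protocol article gives a complete set of inputs.

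- Power and level: "the sample size calculation was based on having 80% power at the 5% significance level". Whether the test is one- or two-sided is not stated.
- Effect: the aim is "to detect a difference in mean post-treatment improvement of 3 units or more on the Roland-Morris Back Pain Questionnaire".
- Variability: "assuming that the standard deviation of the improvement is 6.1 units in both groups".
- Result: "In order to ensure sufficient power to detect such a difference, a sample size of 60 is needed for each arm".
- Attrition: after a 15% allowance, "we aim to include 140 participants (70 per group) in the study and expect to have complete data for about 120 participants following dropouts".

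The abstract (Methods and design) gives equal allocation: "patients are randomised equally to the intervention or control condition within each of the seven trial locations". The Quantitative analysis section plans a linear mixed model that adjusts for baseline, treatment centre and, as necessary, patient characteristics. The Sample size section makes no reference to that adjustment.

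**The concern.** Every quantity needed for a standard two-sample calculation is printed, so the result can be checked directly, and 60 is too small. The 60 then carries through the rest of the section: 70 per group is 60 inflated for attrition, and the expected 120 completers are 60 per arm. The attrition step is not a second error; it simply starts from a figure that is too low.

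At stake is the headline design claim for the primary outcome. If the trial finds no difference, readers will judge that result against a claimed 20% chance of missing a true 3-point effect. On the protocol's own inputs that chance is about 24%.

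**Working it through.** **Inputs.** From the Sample size section: difference δ = 3, SD of improvement σ = 6.1 in both arms, α = 0.05, power 0.80, 60 analysed per arm, 15% attrition. From the abstract: 1:1 allocation. Assumption: a two-sided test, with one-sided tried as a variant.

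**Attempt to reproduce 60.** Using n per arm = 2 (z₁₋α/₂ + z₁₋β)² (σ/δ)²:

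- Normal approximation, two-sided: 2 × (1.960 + 0.842)² × (6.1/3)² = 64.9, so 65 per arm.
- t-test (noncentral t), two-sided, standardised difference 3/6.1 = 0.492: 65.9, so 66 per arm.

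Other readings of the same inputs:

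| Variant | n per arm |
|---|---|
| One-sided 5%, 80% power | 52 |
| Two-sided, effect size rounded to 0.5 (or SD rounded to 6) | 63 to 64 |
| Plan's figure | 60 |

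None of these gives 60.

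**Power at the planned numbers** (two-sided, δ = 3, σ = 6.1). For 60 per arm the standard error is 6.1 × √(2/60) = 1.114, and 3/1.114 = 2.694. Normal-approximation power is Φ(2.694 − 1.960) = 76.8%.

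| Analysed per arm | Power, t-test | Power, normal |
|---|---|---|
| 59.5 (70 × 0.85) | 75.8% | 76.5% |
| 60 | 76.2% | 76.8% |
| 65 | 79.5% | 80.1% |
| 66 | 80.1% | 80.7% |
| 70 (no attrition) | 82.4% | 82.9% |

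**What would make 60 sufficient.** At 60 per arm and 80% power:

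- With σ = 6.1, the detectable difference is 3.15 (t-test) or 3.12 (normal).
- With δ = 3, the SD must be no more than 5.82 (t-test) or 5.87 (normal).

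**Attrition.** The plan's own step is consistent: 60/0.85 = 70.6, and 70 × 0.85 = 59.5, in line with about 120 completers. From the recomputed base, 65/0.85 = 76.5 and 66/0.85 = 77.6. That is 77 to 78 per arm, or 154 to 156 randomised, against 140 planned.

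**Effect of baseline adjustment.** The documents give no baseline to post-treatment correlation r, so a range is assumed. With equal SDs at the two times, the residual SD after adjustment is 6.1 × √((1 + r)/2).

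| r (assumed) | Residual SD | Power at 60 per arm (t-test) |
|---|---|---|
| 0.3 | 4.92 | 91% |
| 0.5 | 5.28 | 87% |
| 0.7 | 5.62 | 83% |
| 0.8 | 5.79 | 80% |

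Under that assumption, power falls below 80% once r exceeds about 0.82.

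**The case against.** The strongest reply is that the trial will not be analysed by an unadjusted comparison of change scores. The planned model adjusts for baseline, and over a wide range of plausible correlations that brings power at 60 per arm to 80% or more. This stands as a limit on the consequence: the 24% miss rate, and the 77 to 78 per arm to randomise, belong to the unadjusted two-sided calculation and are not established for the planned analysis. It does not rescue the printed figure, because the Sample size section rests on the unadjusted SD of improvement and states neither a correlation nor a residual SD.

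Second, two-sidedness is an assumption. With a one-sided 5% test, 60 per arm would have about 85% power, so the 80% claim would be met. But 60 would then not be the number needed (52 would), and nothing in the article says the test is one-sided.

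Third, 70 per arm would give about 82%. That requires no attrition, whereas the section itself expects only about 120 participants with complete data.

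Finally, the shortfall is modest: 3.8 percentage points of power, or 0.15 Roland-Morris points of detectable difference. Interpretation of the trial will rest mainly on the estimate and its confidence interval. That is fair, and it bears on how much weight the point carries, not on whether the figure is right.

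**Conclusion.** The concern holds. On the inputs printed in the Sample size section, 60 per arm delivers about 76% power, and 80% requires 65 to 66 analysed per arm. The figure is therefore 5 to 6 per arm too low, and none of the standard variants tried reproduces it. The conclusion assumes a two-sided 5% test and an unadjusted comparison of mean improvement, which is the calculation the section describes. The true power of the planned baseline-adjusted analysis may be 80% or higher, but it cannot be determined from the document. This is an error in a stated design figure, and it does not affect the randomisation, the conduct of the trial or the choice of analysis.

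**What to change.** Correct the Sample size section in one of two ways, stating in either case that the test is two-sided if that is intended.

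1. Keep the inputs and restate the result: about 120 analysed participants give about 76% power for a 3-point difference at SD 6.1, or 80% power for 3.15 points.
2. Rebase the calculation on the planned baseline-adjusted model, giving the assumed baseline to post-treatment correlation and its source, and a residual SD of 5.8 or less. As an illustration only, equal SDs and r = 0.5 give a residual SD of 5.28 and about 87% power at 60 per arm.

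The cost is wording only: the claimed power becomes slightly less favourable, or is properly justified. The Trial status section reports that recruitment was completed in May 2013, so no extra enrolment is proposed.

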### Screening measures

Patients who have returned written consent forms will be asked to complete a postal questionnaire pack containing measures of psychosocial risk factors and economic evaluation. Data will be collected from patients at baseline (prerandomisation), midtreatment (intervention group only, as this is part of the PGAP protocol), posttreatment (or at 10 weeks postbaseline for controls) and 12-month follow-up via postal questionnaire.

The primary outcome measure will be post-intervention changes in pain disability and work status post-treatment. Specific outcome measures were selected on the basis of the targeted psychosocial risk factors and on the Initiative on Methods, Measurement, and Pain Assessment in Clinical Trials (IMMPACT) recommendations for outcome measures for chronic pain clinical trials [24]. These measures include the following: (1) Roland-Morris Disability Questionnaire [25], (2) Chronic Pain Grade Questionnaire [26], (3) Short-Form McGill Pain Questionnaire [27], (4) Pain Catastrophizing Scale [28], (5) Fear-Avoidance Beliefs Questionnaire [29], (6) Hospital Anxiety and Depression Scale: Depression Subscale [30] and (7) Fear and Fatigue Questionnaire [12].

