### Randomisation and treatment allocation

Eligible participants (that is, those who show elevated psychosocial risk factors) will be randomly assigned by computer-generated block randomisation to ‘intervention’ (PGAP sessions plus MTAU) or ‘control’ (MTAU only). We expect 20 participants to take part in the trial in each of the seven trial centres. Therefore, block randomisation with variable block sizes is used to minimize the occurrence of chance imbalance in allocation to treatment and control and to preserve unpredictability. The sequence of the different blocks is predetermined by an independent researcher not involved in the trial and concealed to all investigators. The blocks are generated separately for the different study sites so that stratification according to trial centre can be performed. It was decided to stratify on trial centre only for pragmatic reasons. Stratifying on additional variables, although useful, would have called for a larger sample. As each treating psychologist was seeing these trial patients in addition to their usual caseload, a limit was placed on the number of patients each clinician would be asked to see, thus limiting stratification.

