### Progressive Goal Attainment Program

The PGAP is a 10-week one-to-one rehabilitation programme delivered in this trial by clinical psychologists. Each session is 1 hour long. The intervention was specifically designed to assist those individuals with thought patterns and behaviours which are known to increase risk for chronic disability. Patients are offered a maximum of 10 individual appointments with the PGAP psychologist. At their first appointment, patients receive an instructional DVD which orientates them to the PGAP and explains the importance of activity mobilization. Through the course of the treatment programme, the PGAP clinician assists the patient in identifying ways to increase activity involvement. Working with the PGAP clinician, the patient develops an activity schedule that is designed to keep him or her as active as possible. This may include household activities, running errands and social and recreational activities. A central element is a programme of regular walking. The patient’s spouse or partner is invited to participate in activity planning so that he or she is aware of the program that is being developed for the patient.

In the second phase of the program, the patient develops skills to overcome fears of reinjury and learns to monitor and modify self-defeating thinking that may accompany pain. The patient is taught methods of approaching physical activity in a way that minimizes worries and concerns about potential reinjury by using cognitive behavioural therapy strategies. Specifically, the programme addresses functional activity scheduling, activity pacing and psychological obstacles to progress such as fear of movement and reinjury, pain catastrophizing and the impact of negative or pessimistic thinking on emotional well-being and activity level. Finally, the patient learns communication skills and problem-solving strategies that will assist him or her in meeting the challenges brought on by the injury.

A total of 11 clinical psychologists employed in the public health service were trained to deliver the PGAP. This training involved attending a 2-day workshop delivered by the developer of the intervention ([name], McGill University, Montreal, QC, Canada). The psychologists involved in the trial are spread geographically throughout the Republic of Ireland and will see patients as part of this trial in their usual clinics.

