Patients who have been randomly assigned to the intervention condition are contacted by the researcher involved in the trial to discuss their participation. An appointment is arranged with a PGAP psychologist who is geographically closest to the patient. Each patient is seen for a maximum of 10 hourlong one-to-one appointments with the PGAP psychologist. In parallel with these sessions, patients are free to access their GP and any other healthcare professional as usual. Patients are offered a maximum of 10 sessions with the clinical psychologist as part of the PGAP. Each patient is given a copy of the *Client Manual*, a workbook of exercises to be completed as part of the programme. The programme may be terminated earlier if the patient is able to return to work before attending all 10 sessions. Termination of treatment before the end of the 10 sessions will be at the discretion of each psychologist in consultation with the patient and patient’s GP.

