### Control condition

Patients allocated to the control condition do not receive the PGAP. The patient is contacted by the researcher to explain that they have been allocated to the control condition and what this means. This gives the patient an opportunity to ask questions. This step is followed by written confirmation of the patient’s allocation to the control group. Patients in the control condition are free to access all healthcare services as usual. Patients who are randomised to the control condition will not be precluded from enrolling in a psychological pain management programme for the duration of this trial. If this happens, however, their data will be excluded from analysis. Participants in the control condition are sent assessment measures at baseline and at 10 weeks postbaseline. It is recognized that GP care will vary from individual to individual.

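### The primary assessment falls at 10 weeks after a pre-randomisation baseline in controls but at an undated end of treatment in the PGAP arm, so elapsed time differs between arms and mixes with the treatment effect

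*Protocol article*

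**What the plan says.** The Screening measures section of the protocol article sets the assessment times. The start of the clock comes before allocation: "Data will be collected from patients at baseline (prerandomisation), midtreatment (intervention group only, as this is part of the PGAP protocol". The main follow-up is then "posttreatment (or at 10 weeks postbaseline for controls) and 12-month follow-up via postal questionnaire". The Control condition section repeats the control time: "Participants in the control condition are sent assessment measures at baseline and at 10 weeks postbaseline". No week or window is given for the PGAP arm.

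The Progressive Goal Attainment Program section gives the nominal length: "The PGAP is a 10-week one-to-one rehabilitation programme delivered in this trial by clinical psychologists". The abstract says that PGAP patients "attend a maximum of 10 weekly individual sessions of structured active rehabilitation in addition to usual care". Treatment begins only after allocation, when the researcher has contacted the patient and "An appointment is arranged with a PGAP psychologist who is geographically closest to the patient". It can also end early: "The programme may be terminated earlier if the patient is able to return to work before attending all 10 sessions". Early ending is left to the psychologist's judgement, in consultation with the patient and the GP.

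The abstract bases the primary analysis on change in the Roland-Morris Disability Questionnaire (RMDQ) after treatment. Screening measures names disability and work status together as the primary outcome. The Quantitative analysis section specifies a linear mixed model of change before and after the intervention, adjusted for baseline, centre and patient characteristics. Elapsed time is not among the adjustments it names.

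**The concern.** A randomised comparison of change from baseline is fair only if both arms are observed over the same interval. Here the control interval is fixed at 10 weeks. The PGAP interval is the time taken to score the questionnaires, randomise, make contact and book, plus the length of the course. If disability changes over time irrespective of treatment, the arm measured later shows more of that change, and the difference is attributed to PGAP. Some such change is plausible, because Inclusion criteria admits patients with pain of as little as 6 weeks' duration.

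A second route is possible. If the post-treatment questionnaire goes out when treatment actually ends, a patient who stops on returning to work is measured sooner, at a time set by an outcome. Controls have no such trigger.

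What is at stake is the primary result: an observed difference could not be cleanly separated from unequal follow-up time.

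**Working it through.** **Is the interval unequal on the article's own terms?** Count weeks from the pre-randomisation baseline.

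- Control assessment: week 10 (Screening measures; Control condition).
- PGAP assessment after a full course: week D + 10 + M. D is the time from baseline to the first session, and M is any weeks missed during the course. The article gives neither.
- Difference: w = (D + 10 + M) − 10 = D + M.

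D includes scoring the risk factors (Medication and health service use), randomisation, contact by the researcher and booking, so it is above zero. If the course is instead counted strictly as ten weekly sessions, the tenth falls 9 weeks after the first and w = D + M − 1. This is still positive once start-up and missed weeks together exceed one week. If a patient stops early and is assessed at that point, w can be negative.

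**Size of the bias.** Let s be an improvement in RMDQ points per week common to both arms. The bias in the difference between arms is b = s × w. The article gives no figure for s or w, so both are assumed: s from 0.05 to 0.15, and w from 2 to 8 weeks later, or 2 to 4 weeks earlier for the reverse case.

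**Scale.** From Sample size: target difference 3, standard deviation (SD) of improvement 6.1, 60 complete per arm. The standard error of the difference is 6.1 × √(2/60) = 1.114. The plan's own figure does not quite reproduce: a two-sided 5% test with 80% power needs 2 × (1.960 + 0.842)² × 6.1² / 3² = 64.9, so 65 per arm, and 60 per arm gives 76.8% power. That is a separate matter; 76.8% serves below only as the reference power.

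The false-positive rate, with no true effect, is 1 − Φ(1.96 − b/1.114) + Φ(−1.96 − b/1.114). Power uses the same expression with 3 + b in place of b.

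| s (points/week) | w (weeks) | b (points) | b as % of 3 | False-positive rate, two-sided | Power for a true 3 points |
|---|---|---|---|---|---|
| 0.05 | 2 | 0.1 | 3% | 5.1% | 79% |
| 0.10 | 4 | 0.4 | 13% | 6.5% | 86% |
| 0.15 | 4 | 0.6 | 20% | 8.4% | 90% |
| 0.10 | 8 | 0.8 | 27% | 11.1% | 93% |
| 0.15 | 8 | 1.2 | 40% | 19.0% | 96% |
| 0.05 | −2 | −0.1 | −3% | 5.1% | 74% |
| 0.15 | −4 | −0.6 | −20% | 8.4% | 58% |

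In the rows with positive b, rejections tilt towards PGAP, and the higher power is not a gain because it comes from bias. In the rows with negative b the tilt is against PGAP.

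**Does the stated model remove it?** Baseline score, centre and patient characteristics are all fixed before treatment. None carries the interval between the two measurements. A before-and-after coding of time treats a control at week 10 and a PGAP patient at a later week as the same occasion.

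**The case against.** The strongest reply is that the size is wholly assumed, and parts of the assumption look generous. An improvement of 0.15 points per week, if sustained for a year, is 0.15 × 52 = 7.8 points, or 2.6 times the target effect, without the programme. The Background section says that 60% to 80% of those consulting for chronic pain still have pain and disability a year later. The low end, 0.1 points, hardly matters. This stands: the upper figures are a bound under brisk early improvement, not an estimate.

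A reader might infer long waits from the remark "As each treating psychologist was seeing these trial patients in addition to their usual caseload". The article does not support that. It says usual caseload, not full, and the same sentence caps the number of patients per clinician. With 11 trained psychologists and 70 PGAP patients, the average is 70/11, or about 6 each. A start-up lag follows from the sequence of steps; a long one does not.

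A reader might also infer that patients who return to work are measured at their moment of success. No sentence says that early stopping triggers the questionnaire. Data are collected by post from the coordinating centre, so a nominal 10-week mailing is equally possible. In that case the outcome-dependent element disappears and only the start-up lag remains.

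Nor does selection on elevated scores by itself create a difference between arms. Regression to the mean is largely shared by randomised groups and does not simply build up with each extra week.

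Finally, the Control condition section omits the 12-month questionnaire, which could be read as no long-term follow-up for controls. Screening measures attaches the control exception only to the post-treatment point, and Medication and health service use gives follow-up for all patients. This is a wording point.

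The defence that windows and time coding belong in an unseen analysis plan does not answer the main point. The article itself fixes the schedule, and fixes it unequally. An analysis plan could examine the consequence but could not make the measurement times equal.

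**Conclusion.** The point holds in a limited form. The article sets different clocks for the primary assessment, and PGAP patients who complete the course are assessed later than controls by an unstated lag. The named adjustments do not correct for this. Whether timing also depends on outcome turns on what post-treatment means for early stoppers, which the article leaves open.

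The size and direction of the bias cannot be fixed from the article. Under the assumed 2 to 8 weeks and 0.05 to 0.15 points per week, it is 0.1 to 1.2 RMDQ points in favour of PGAP, and the two-sided false-positive rate is between about 5% and 19%. If PGAP is assessed 2 to 4 weeks earlier, the bias is 0.1 to 0.6 points against PGAP. The point deserves correction because it touches the primary endpoint and a common schedule removes it, not because a large bias has been shown.

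**What to change.** **Schedule.** Assess both arms at the same fixed time from randomisation, with the same window. Choose the time so that the 10-session course is normally complete, and apply it whatever the number of sessions attended. Anchor the 12-month assessment to randomisation in both arms. This changes only when questionnaires are sent; the rule for ending treatment is untouched. Add the 12-month questionnaire to the Control condition text for consistency.

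**Data already collected.** Trial status says that recruitment closed in May 2013 with follow-up collection ongoing, so most post-treatment assessments can no longer be re-timed. State when post-treatment questionnaires were sent in the PGAP arm, including to early stoppers. Where dates were recorded, report elapsed time from randomisation by arm. Add a sensitivity analysis for elapsed time, for example the RMDQ difference under a range of assumed weekly drifts, or actual time in the mixed model. State its limits. With controls all near 10 weeks, time is nearly confounded with arm, so the model has little information to separate the two. Restricting to a common window conditions on timing that arises after randomisation and may introduce selection.

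**Cost.** A change to the mailing schedule for assessments still to come, and one extra analysis. Under a fixed schedule, some PGAP patients would be measured just before or just after their last session.
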